### Interim analyses {21b}

We do not plan to conduct any interim analyses.

### Methods for additional analyses (e.g., subgroup analyses) {20b}

We will estimate complier average causal effects (CACE) on the primary outcomes. We will also conduct subgroup analyses to examine heterogeneous intervention effects, provided that sufficient sample sizes can be recruited in each group. The variables of interest are prior skill levels in writing ability, critical thinking ability, and English language ability, as well as motivation. Each of these variables will be examined independently. Additionally, we will take advantage of the pupil size data collected throughout the writing task to explore the intervention effect on cognitive effort across various self-allocated sub-tasks, such as writing the essay, reading the essay, and prompting ChatGPT.

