### Trial design {8}

Our study is a parallel RCT that compares the effects of using ChatGPT (intervention group) versus not using ChatGPT (control group) in an analytical writing task (Fig. 1). Participants will be randomized in a 1:1 ratio. The study follows an exploratory framework.

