Within the third stage, the participant will first complete a pre-survey. They will then be instructed to read some materials to learn about analytical writing, and then practice what they have learned by writing an analytical essay as their homework assignment. During practice, the instructions will outline the writing prompt, writing requirement, time requirement, grading feedback, and grading rubric. Specifically, the participant will be asked to write a 350–600-word essay stating whether they agree or disagree with the writing prompt. The time requirement will explain that there is no time limit, but participants are recommended to spend 30 min on the task. We intentionally designed the writing task without a time limit to better reflect a typical homework setting, in contrast to an exam setting where time is constrained. This distinction may elicit different writing behaviors and patterns of using AI tools. For grading feedback, the instructions will explain that the participant will receive their writing score, the class average, and writing feedback from expert instructors once the entire experiment ends. Participants in the intervention group can use ChatGPT to support their writing. Specifically, we choose GPT-4 because it has been independently benchmarked for its standalone performance on analytical writing in the Graduate Record Examinations (GRE), as documented in OpenAI’s technical report [31]. This provides a reference point for us to evaluate the analytical writing capabilities during human-generative AI collaboration. Participants in the control group will complete the writing task without AI assistance. After the writing task, the participant will complete a post-survey. The entire study will last for approximately 1.5 h for each participant.

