## Interventions

### Intervention description {11a}

In the intervention group, the computer screen will be set up in a split-screen format. On the left side of the screen, the participant will receive instructions on the writing prompt, writing requirements, time requirements, grading feedback, and the grading rubric. The instructions will also highlight to the participant that they can use ChatGPT in any way they like to assist their writing, and there is no penalty in their writing score for how ChatGPT is used. The right side of the screen will display a blank ChatGPT interface where the participant can prompt questions and receive answers.

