### Explanation for the choice of comparators {6b}

In the control group, as in the intervention group, the computer screen will be set up in a split-screen format. On the left side of the screen, the participant will receive the same instructions on the writing prompt, writing requirements, time requirements, grading feedback, and the grading rubric. Additionally, the instructions will highlight to the participant that they can use a text editor in any way they like to assist their writing. On the right side, instead of ChatGPT, a basic text editor interface will be displayed. In summary, this comparator will keep the split-screen format consistent between the two groups and ensure that participants in the control group will complete the writing task with minimal support.

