### Sample size {14}

To estimate the required sample size, we conducted a simulation analysis on the intervention effect on writing performance using ordinary least squares (OLS) regression. Recent empirical evidence suggests that the effect size of generative AI on writing tasks ranges around Cohen’s *d* = 0.4–0.5, such as [1, 48]. In our simulation analysis, the simulated data assumes normally distributed data, equal and standardized standard deviations between the two conditions, and an anticipated effect size of Cohen’s *d* = 0.45. In the end, our analysis indicated that recruiting a minimum of 160 participants would be necessary to achieve a statistical power greater than 0.8 under an alpha level of 0.05. The simulation was implemented in R, and the corresponding code is available at the Open Science Framework (OSF) via https://osf.io/9jgme/.

We opt to base our sample size estimation on writing performance, but not on the other primary outcome, cognitive effort, for two reasons. First, the effect of generative AI on performance outcomes has been studied [1, 48], but we did not find prior evidence on the effect size of generative AI on cognitive effort using physiological measures. Second, our physiological measure of cognitive effort may likely be powered once the sample size satisfies our behavioral measure of writing performance. Pupillometry studies on cognitive efforts, such as the N-back test, typically recruit 20–50 participants in short, repeated, within-subject trials (e.g., [49]). These studies provide a general estimation of participants needed. Although our study design (i.e., a between-subject RCT) differs from common pupillometry studies, cognitive effort is still a repeated outcome measure using time series pupil data throughout the entire writing process. Repeated outcome measures generally can enhance statistical power by taking into account within-subject variability [50].

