### Implementation {16c}

Randomization was generated in advance of the entire experiment using an R script that allocated participant IDs into either the intervention group or the control group. The randomization algorithm is independent of the researchers who will recruit participants and implement the protocol.

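### The exploratory sub-task analysis calls its target the intervention effect, but controls cannot prompt ChatGPT, and time spent writing or reading is chosen after randomisation

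*Protocol article*

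**What the plan says.** The section on additional analyses {20b} plans to use the pupil data recorded during the task to "explore the intervention effect on cognitive effort across various self-allocated sub-tasks, such as writing the essay, reading the essay, and prompting ChatGPT".

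Four other places determine what that can mean:

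- **Control arm.** Explanation for the choice of comparators {6b}: "instead of ChatGPT, a basic text editor interface will be displayed". Trial design {8}: "Participants in the control group will complete the writing task without AI assistance".
- **Intervention arm.** Intervention description {11a}: participants are told "they can use ChatGPT in any way they like to assist their writing", with no score penalty for how they use it.
- **Time on task.** Trial design {8}: "there is no time limit, but participants are recommended to spend 30 min on the task".
- **What is randomised.** Implementation {16c}: the script "allocated participant IDs into either the intervention group or the control group". Persons are randomised and sub-tasks are not.

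The primary analysis of effort, in Statistical methods {20a}, is a different quantity: mean pupil change over the whole writing process, compared between arms by intention to treat. Trial design {8} also states: "The study follows an exploratory framework".

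**The concern.** In {20a} the term intervention effect means the difference between randomised arms. Section {20b} carries the same term over to sub-tasks, where it does not fit, for two reasons.

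First, prompting ChatGPT is something only one arm can do. A difference between arms needs data in both.

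Second, writing and reading are available to both arms, but a participant with ChatGPT can hand over much of the drafting and a control cannot. Those in the intervention arm who still write a good deal themselves may differ from the rest in how much effort they habitually invest. Setting them against nearly all controls conditions on behaviour that the intervention can change.

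At stake is the interpretation of the process data, which the Discussion presents as a main strength of the study. A difference in effort while writing could arise from who chose to write, with no effect of ChatGPT on effort during writing, and still carry the label of an intervention effect.

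**Working it through.** **1. The plan's own figure, for the number per arm.** Sample size {14} states that "recruiting a minimum of 160 participants would be necessary to achieve a statistical power greater than 0.8 under an alpha level of 0.05", with d = 0.45 and SD 1. Assuming a two-sided test, n per arm = 2 × (1.96 + 0.84)² / 0.45² = 77.5, so 78 per arm and 156 in total, in line with 160. Power at 80 per arm is 0.81. The figure is reproduced. The point does not depend on it, and it serves only to give about 80 per arm.

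**2. Prompting ChatGPT.** Section {20b} names it as a sub-task; {6b} and {8} give controls no ChatGPT. Controls with pupil data while prompting: 0 of about 80, by design. The between-arm difference cannot be computed. No assumption is needed.

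**3. Writing and reading.** Only participant IDs are randomised {16c}, use of ChatGPT is free {11a}, there is no time limit {8}, and {20b} itself calls the sub-tasks self-allocated. Entry into a sub-task and the time spent in it therefore come after randomisation and can depend on the arm.

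**4. How large selection could be.** The documents give no inputs for this, so all of these are assumptions: no true effect on effort while writing; all controls contribute writing data; a share p of the intervention arm contributes usable writing data; and a normally distributed tendency to write, correlated ρ with a person's effort level, decides who does. The mean of the upper fraction p of a standard normal is φ(z)/p, where z is the cut-off, so the spurious difference in SD units is ρ × φ(z)/p.

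| Share p | φ(z) | φ(z)/p | ρ = 0.3 | ρ = 0.5 |
|---|---|---|---|---|
| 0.95 | 0.103 | 0.109 | 0.03 | 0.05 |
| 0.90 | 0.175 | 0.195 | 0.06 | 0.10 |
| 0.80 | 0.280 | 0.35 | 0.105 | 0.175 |
| 0.70 | 0.348 | 0.497 | 0.15 | 0.25 |
| 0.50 | 0.399 | 0.80 | 0.24 | 0.40 |

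**5. Check by simulation.** With 80 per arm, no true effect, 4,000 repeats per setting and a Welch t-test at nominal 5%:

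| Share p | ρ | Mean spurious difference (SD) | Rejections |
|---|---|---|---|
| 0.9 | 0.3 | 0.06 | 6.6% |
| 0.9 | 0.5 | 0.10 | 9.3% |
| 0.7 | 0.3 | 0.15 | 13.7% |
| 0.7 | 0.5 | 0.25 | 31.2% |
| 0.5 | 0.3 | 0.24 | 24.1% |
| 0.5 | 0.5 | 0.40 | 56.8% |

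Formula and simulation agree. The sign follows from assuming that people inclined to write also invest more effort; the opposite assumption reverses it.

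**The case against.** The strongest reply is that {20b} offers one exploratory sentence. It uses the verb explore, gives the sub-tasks as examples, and sits under additional analyses in a study that calls itself exploratory. Across sub-tasks could mean a breakdown of where in the task effort arises, with prompting described in the one arm where it occurs. The word self-allocated already concedes that sub-tasks are not randomised. Nothing here feeds a primary or secondary outcome, the sample size or the alpha split. Definitions and denominators for a gaze-based segmentation may properly sit in an analysis plan that is not shown.

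Most of this stands as a limit on severity. It does not remove the point, because the sentence names the target as the intervention effect and lists a sub-task that one arm cannot perform. That is a matter of what is stated, not of missing detail.

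Three stronger readings go beyond the documents:

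- *That the plan commits to a separate causal contrast for each sub-task and will report it as causal.* Section {20b} lists no contrasts and promises no such reporting. The Discussion speaks of insight into how cognition evolves over a task, which describes process.
- *That a substantial bias is to be expected.* The shares and correlations above are assumptions. Everyone must submit an essay of 350–600 words and gaze is recorded throughout, so nearly all participants may contribute writing data. Selection of persons would then be small, although the content and duration of writing could still differ by arm. The d = 0.45 in {14} concerns writing performance and is no direct yardstick for pupil-based effort.
- *That the primary effort result is compromised.* It uses the whole-task mean and does not depend on sub-tasks.

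**Conclusion.** The point holds within those limits. For prompting ChatGPT the between-arm effect does not exist; this follows from the design alone and is certain. For writing and reading, contrasts between arms can be computed but randomisation does not protect them; this follows from free use of ChatGPT, the absence of a time limit and randomisation by person.

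The size of any resulting bias is unknown. On the stated assumptions it ranges from about 0.03–0.06 SD (90–95% of the intervention arm writing, correlation 0.3) to about 0.40 SD (half writing, correlation 0.5). The intention-to-treat comparison of whole-task mean pupil change is unaffected. This is a cheap correction to an exploratory analysis, worth making before results are seen.

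**What to change.** In {20b}, or in the analysis plan with a matching change in {20b}:

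1. Keep the term intervention effect for the whole-task mean pupil change.
2. Analyse prompting ChatGPT only as a within-person contrast in the intervention arm, for example against the same participant's own writing.
3. For writing and reading, report effort by arm as descriptive and non-randomised, with the number of participants and the time contributing in each arm.
4. If a randomised sub-task comparison is wanted, compare time or share of time in the shared sub-tasks, counting zero when a sub-task was not done, among all randomised participants with usable recordings. Unusable recordings must be excepted because {20a} excludes participants with poor-quality pupil data.

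The cost is a few sentences and, for item 4, one extra exploratory summary. The gaze data, ChatGPT logs and text-editor data it needs are already collected under {18a}. The downside is that sub-task pupil contrasts lose their causal label.

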### Methods in analysis to handle protocol non-adherence and any statistical methods to handle missing data {20c}

During the lab experiment, we will monitor and control for missingness in the survey data due to non-adherence under 20%. If the missingness is less than 5%, we will conduct a complete case analysis, which removes participants with missing responses [57, 58]. If the missingness falls between 5 and 20%, we will apply multiple imputation using the rest of the survey data [59].

### Plans to give access to the full protocol, participant-level data, and statistical code {31c}

This document is the full protocol. Anyone interested in aggregated versions of the data and the statistical code may contact the corresponding author. The consent form and other materials can be accessed via OSF: https://osf.io/9jgme/.

## Oversight and monitoring

### Composition of the coordinating center and trial steering committee {5d}

The coordinating center will be based at the Heidelberg Institute for Global Health (HIGH). The day-to-day experiment coordination will be managed by the study team at the Core Facility for Neuroscience of Self-Regulation (CNSR). The principal investigator will provide oversight of the study. The data manager will be responsible for organizing data collection and ensuring the integrity and quality of the data. The study coordinator will oversee participant recruitment, study visits, and weekly feedback reports. There is no trial steering committee or stakeholder and public involvement group.

### Composition of the data monitoring committee, its role and reporting structure {21a}

The study will not include a data monitoring committee separate from the study team because there will be no interim data analyses. The study team is independent from the sponsor of the trial and competing interests.

### Adverse event reporting and harms {22}

This trial is a lab experiment that asks participants to complete a writing task. It is very unlikely to cause adverse events.

### Frequency and plans for auditing trial conduct {23}

Not applicable. This study is a small-scale lab experiment that does not require external auditing.

### Plans for communicating important protocol amendments to relevant parties (e.g., trial participants, ethical committees) {25}

In the event of substantial amendment, this will be reported to the Ethics Committee at Heidelberg Medical Faculty. Non-significant amendments will be documented and updated in the online trial registries. Additional documents will be uploaded to the OSF.

### Dissemination plans {31a}

The results of this study will be disseminated through presentations at international conferences and publications in peer-reviewed journals.

## Discussion

Since the public release of ChatGPT in 2022, there have been heated discussions on the societal implications of generative AI. Concerns and promises have both been raised about its potential effect on human cognition when such tools are widely integrated into daily tasks [6, 15]. In this study, we propose to evaluate the effects of generative AI use on human cognition and task performance, in the context of a hypothetical analytical writing assignment undertaken by college students.

The main innovation of our study is using multi-modal data to evaluate the effects of generative AI. We will collect psychophysiological data throughout the writing process using state-of-the-art neuroscience technologies. Specifically, we will use the Tobii Pro Fusion eye tracker to capture pupil size changes and gaze patterns. We will use the NirSport2 fNIRS system to measure brain activity. These data will then be combined and analyzed with behavioral data and self-reported attitudinal data collected in the pre- and post-surveys. The multi-modality of the data provides a few advantages. First, collecting data from different modalities will give us a more comprehensive understanding of the effects of generative AI. For example, combining psychophysiological measures with self-reported measures can provide insights into both the internal cognitive processes and observable behaviors of participants. Second, multi-modal data will allow us to validate findings from different data sources. Third, the real-time measures captured in this study reflect dynamic changes as tasks are performed. These data will provide deeper insights into how cognitive processes evolve during different phases of a task.

Our study design ensures a high internal validity due to the controlled lab setting. However, this approach has limitations in generalizability. The recruitment process relies on a convenience sampling strategy, as the experiment requires equipment located at the university’s research lab. As a result, participants may represent a WEIRD (Western, Educated, Industrialized, Rich, Democratic) population and may not represent the impact of generative AI use in a broader, more diverse population. Moreover, participants in the experiment may not behave as they would in real-world settings. In our study, we will carefully control the motivational context for the writing task. Specifically, we will measure participants’ general motivation to achieve a high score before they start working on the writing task and will account for this variation in our regression models. We will also control for external incentives by framing the experiment setting as a hypothetical writing class and by informing participants that they will receive their performance scores, the class average, and the instructor’s feedback after completing the task. This design aims to reflect real-life motivational settings for completing homework assignments. Unlike in other experimental research evaluating the effects of generative AI (e.g., [1, 4]), we opt not to incentivize better performance monetarily, as this is not suitable for our study context.

## Data Availability

The final trial data are deidentified and will be stored on a university-owned, encrypted cloud storage service. The study investigators own and have complete control over the research data. Open Access funding enabled and organized by Projekt DEAL.

## Abbreviations

AI: Artificial intelligence
SAP: Standard assessment paradigm
RCT: Randomized controlled trial
fNIRS: Functional near-infrared spectroscopy
GRE: Graduate Record Examination
ETS: Educational Testing Service
HbO: Oxyhemoglobin
PFC: Prefrontal cortex
SMA: Supplementary motor area
NASA-TLX: National Aeronautics and Space Administration-task load index
PASA: Primary Appraisal Secondary Appraisal
OLS: Ordinary least squares
OSF: Open Science Framework
CV: Coefficient of variation
MBLL: Modified Beer-Lambert law
TDDR: Temporal Derivative Distribution Repair
CACE: Complier average causal effects
HIGH: Heidelberg Institute for Global Health
CNSR: Core Facility for Neuroscience of Self-Regulation
WEIRD: Western, Educated, Industrialized, Rich, Democratic
